### Data analysis plan (by objective)

Counseling completion rates will be calculated; we will treat each interpreting arm (RSMI, RCMI) as a single stage design and will assess each separately for feasibility (*primary outcome*). We will calculate frequencies and percentages to summarize recruitment, randomization, retention, acceptability (*secondary outcome*), and usability across all 3 arms (RSMI, RCMI, and bilingual provider). Based on the calculation outlined by Khan, Sarker, and Hackshaw [58], observing 11 or more successes out of 15 in a given arm would allow us to be sufficiently confident that the population feasibility of the corresponding interpretation mode is 90% against a null of 40%. In our calculations, we have set our statistical power to 90% and our Type I error rate to 0.025 to reduce the chance of false discovery. This provides us with sufficient combined statistical power, assuming the two tests are independent.We will summarize (1) therapeutic alliance scores and MCP-Ch content comprehension at T4 across all 3 arms (RSMI, RCMI, and bilingual provider) and (2) number and nature of clinically significant interpreting errors in MCP-Ch Session 1 across the interpreting arms (RSMI, RCMI) (*secondary outcomes*). We will also summarize treatment credibility/expectancy at T2 and differences in post- vs. pre-intervention distress, spiritual well-being, quality of life, anxiety and depression, meaning-in-life, hopelessness by arm (*exploratory outcomes*). These descriptive summaries by arm will provide preliminary indications of whether delivery of psycho-oncology counseling via RSMI or RCMI may potentially achieve clinically significant benefits, which will aid in the design of, and be further assessed in, a subsequent fully powered trial [29]. We will assess baseline contextual factors at T1 (e.g., digital health care literacy, level of English proficiency) to examine whether therapeutic alliance and MCP-Ch content comprehension scores differ by these variables. We will use an error analysis tool developed by Gany et al. [21] to obtain the number and nature of clinically significant errors in MCP-Ch Session 1. Specifically, a panel of 2–4 psycho-oncology clinicians blinded to the interpreting method (i.e., RSMI or RCMI) will review and code transcripts. They will independently code each script to identify clinically significant content and meet to reconcile any differences in their selection of clinically significant content. Examples of potentially clinically significant content include history of cancer diagnosis, past psychiatric history, MCP-Ch session exercises, and plans for future visits. Once all clinically significant content has been identified, a second blinded panel of 2–4 bilingual coders will independently code clinically significant content to identify interpreting errors, yielding a total count of clinically significant interpreting errors. To ensure rigor, coders on both panels will first separately conduct preliminary analyses on a subset of transcripts using the described protocol. Interrater reliability will be assessed by calculating percent agreement. Consensus meetings will be held to adjudicate disagreements and refine error categories and the analytic approach as needed until strong interrater reliability is reached (i.e., *k* = 0.80), at which point coders will commence coding of the remaining transcripts.To assess our semi-structured interviews with “extreme responders,” we will use thematic content analysis [59] to derive insights directly from participants’ narratives, following established guidelines for conducting rigorous qualitative research [60]. First, coders will each read a subset of interviews and develop codes to characterize responses. Coders will then meet to establish an initial codebook, which will be used to code the remaining interviews. Regular consensus meetings will be held to confirm the reliability of coding. The codebook will be iteratively revised as new codes emerge, and codes will be summarized into themes. Prominent themes will include those observed across the majority of interviews as well as key divergences between sub-groups. Findings will be integrated using NVivo [61], which enables qualitative and quantitative data to be paired by participant and in summary format. The coded qualitative data will be explored in relationship to participant outcomes, baseline characteristics, contextual factors, and study arm to further elucidate barriers and facilitators to the implementation of remote interpreting in the psycho-oncology setting.

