The majority of patients with LEP who access mental health care do so through medical interpreters, given a national shortage of bilingual mental health professionals [19]. Typically, medical interpretation is consecutive (interpreting is provided once a speaker has finished speaking) [20]. RSMI or “United Nations-style” interpreting is similar to a voice-over and is provided remotely by trained medical interpreters [20]. RSMI is likely superior to consecutive interpreting methods due to increased efficiency [21, 22], fewer clinically significant medical errors [21, 22], and enabling a more private and dyadic clinical encounter [21, 23]. By contrast, the most commonly employed interpreting strategy, Remote Consecutive Medical Interpreting (RCMI), can interfere with the collaborative relationship between patient and therapist (i.e., therapeutic alliance) [24], one of the most robust predictors of psychosocial intervention outcomes [25]. In addition, consecutive interpreting can impede the natural flow of communication, as interpreters pace their interlocutors. Yet to our knowledge, RSMI has not yet been studied in the telemental health context; a systematic review on the use of interpreters in mental health found no quantitative studies on interpreter accuracy nor on the influence of interpretation modes on the therapist–patient relationship [26].

To address these limitations, INTERPRET-PSY is a mixed method, explanatory sequential (QUANT qual), 3-arm pilot randomized controlled trial (RCT) developed to determine whether RSMI is feasible and acceptable in comparison to usual care (RCMI) and “gold standard” care (bilingual provider) in delivering psycho-oncology counseling to Mandarin-speaking Chinese cancer patients with LEP.

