### Key study objectives

Assess the feasibility of interpreting modes in delivering counseling sessions to Chinese cancer patients with LEP. RSMI and RCMI feasibility will be determined by the completion of ≥5 out of 6 sessions for *n* = 11 per arm (*primary outcome*). We will also collect descriptive data on recruitment/randomization/retention rates; acceptability (*secondary outcome*); and telehealth usability for all 3 arms.Collect pilot data on outcomes central to RSMI and RCMI-enabled psycho-oncology counseling. We will summarize post-intervention scores on therapeutic alliance (Working Alliance Inventory), treatment expectancy (i.e., the degree to which participants expect a good outcome from counseling), and counseling content comprehension by arm (RSMI, RCMI, bilingual provider), and will compare the number of clinically significant interpreting errors in MCP-Ch Session 1 across RSMI and RCMI arms *(secondary outcomes)*. We will also summarize post-intervention scores on psychosocial outcomes (e.g., distress, spiritual well-being, quality of life, anxiety and depression, meaning in life, and hopelessness) by arm (*exploratory outcomes*).To inform “best practices” in telehealth delivery of interpreter-mediated psycho-oncology care. We will complement quantitative outcome data with qualitative data from semi-structured interviews with *n*~ 8 “extreme responders” (~6 per arm, pending saturation) and their interventionists and interpreters (if applicable). Interviews will contextualize outcomes and identify barriers and facilitators to interpreter-mediated communication in counseling.

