## Interventions

### RSMI, RCMI, or bilingual provider

Participants assigned to the (1) RSMI, (2) RCMI, and (3) bilingual provider arms (*n* = 15 per arm) will receive all 6 counseling sessions (for details on these sessions, see below) via an English-speaking interventionist and a RSMI interpreter (i.e., a trained bilingual Mandarin-English interpreter who provides remote interpretation within milliseconds of the original speech, nearly simultaneously, almost like a voiceover); an English-speaking interventionist and a RCMI interpreter (i.e., a trained bilingual Mandarin-English interpreter who provides remote consecutive interpretation—by listening as the primary speaker speaks and interpreting only once the primary speaker has finished); and a bilingual interventionist in Mandarin, respectively. Sessions for all 3 arms will take place using a videoconferencing platform and will be recorded. To promote adherence and retention, participants will receive session reminders 1 week, 3 days, and the day prior to the appointment by phone, text, and/or email (with a link to the videoconferencing platform); participants who cannot attend will be given an option to reschedule. Mandarin-English interpreters will be certified as having native bilingual fluency (speaking, understanding, reading, and writing) and meet performance standards for both consecutive and simultaneous interpreting, since they will serve as both RSMI and RCMI interpreters. They will receive intensive training on professional standards of practice and ethics, medical terminology, and linguistic/cultural responsiveness, and will be required to meet professional interpreter standards before study interpreting.

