### Description of counseling sessions

The six counseling sessions will utilize the Meaning-in-life Counseling Program for Chinese cancer patients (MCP-Ch) [30], a cultural and linguistic adaptation [30–32] of Meaning-Centered Psychotherapy (MCP). Meaning-Centered Psychotherapy (MCP) is a brief, structured, manualized intervention grounded in the work of Viktor Frankl [33]. MCP has demonstrated efficacy in enhancing advanced cancer patients’ sense of meaning-in-life and QOL while decreasing feelings of depression, anxiety, desire for hastened death, and distress in several randomized controlled trials [34–36]; for a conceptual framework of MCP, see Breitbart, 2016 [37]. MCP guides patients on how to access “sources of meaning” during challenging times: (1) historical (significant memories, relationships, and traditions and their impact on one’s sense of meaning), (2) attitudinal (confronting limitations imposed by cancer), (3) creative (engaging in life through one’s pursuits, including work, hobbies, life roles), and (4) experiential (connecting with life through experiences with love, beauty, humor, etc.).

MCP-Ch consists of six 60-min individual sessions delivered over the span of 3–12 weeks, depending on participant availability. Adaptations to MCP for the Chinese population focused on changing content and strategies to reflect the Chinese cultural context (Table 1) [30, 38]. MCP-Ch will be delivered by doctoral student clinician interventionists who will receive intensive training prior to delivering the intervention and regular supervision after each session.

**Table 1 Tab1:** MCP-Ch overview and adaptations

1	Intro to MCP-Ch	Added additional orientation about psychotherapy and addressed confidentiality concerns among undocumented patients; created handouts with MCP-Ch structure and educational information/FAQ to address cancer myths, cancer stigma, and low health literacy
2	Who Am I? Before Cancer and Now	Given Chinese collectivistic cultural values, clarified that one’s identity includes relationships, beliefs, values
3	Your Life Story: Past, Present, and Future	Given death taboo in Chinese culture, replaced “legacy” with “how you wish to be remembered”; added a list of culturally appropriate questions to guide patients in sharing their life story with others

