MCP-Ch Content Comprehension	T8 (Post-intervention)	Secondary	A 10-item, face-valid, investigator-initiated questionnaire. These multiple-choice items assess a participant’s understanding of MCP concepts presented in the MCP-Ch program
Clinically significant interpreting errors in MCP-Ch Session 1	T8 (Post-intervention)	Secondary	The number and nature of clinically significant interpreting errors made in MCP-Ch Session 1 (RCMI, RSMI arms only) will be assessed using an error analysis tool developed by Gany et al. [21] For more details, see Data analysis plan, objective #2
Credibility/Expectancy Questionnaire (CEQ) [43]	T2 (Post-session 1)	Exploratory	The CEQ is a 6-item questionnaire, half of which relates to the subscale of credibility (i.e., how believable, convincing, and logical the treatment is) and the other half to expectancy (i.e., the improvements the patient believes will be achieved). *r* = 0.85. [49]
Distress Thermometer (DT) [44]	T1 (Baseline), T8 (Post-intervention)	Exploratory	The Distress Thermometer (DT) is a single-item scale used to screen cancer patients for the presence of psychological distress with a 0–10 range. *r* = 0.80 [45].*
Spiritual Well-Being Scale (FACIT-Sp) [46]	T1 (Baseline), T8 (Post-intervention)	Exploratory	The Functional Assessment of Chronic Illness Therapy—Spiritual Well-Being Scale (FACIT-Sp) is a 12-item self-report instrument assessing the spiritual well-being of people with chronic and/or life-threatening illnesses. It has three subscales: Peace, Meaning, and Faith. Cronbach’s α = 0.89 [47]*
McGill Quality of Life Questionnaire (MQOL) [48]	T1 (Baseline), T8 (Post-intervention)	Exploratory	The McGill Quality of Life Scale (MQOL) is a 16-item quality of life self-report measure for people with life-threatening illness. It is composed of 4 subscales: physical symptoms, psychological symptoms, outlook on life, and meaningful existence. Cronbach’s α = 0.87 [49]*
Hospital Anxiety and Depression Scale (HADS) [50]	T1 (Baseline), T8 (Post-intervention)	Exploratory	The 14-item Hospital Anxiety and Depression Scale (HADS) measures both anxiety and depression symptoms. Cronbach’s α = 0.93 [51]*
Meaning in Life Questionnaire (MLQ) [52]	T1 (Baseline), T8 (Post-intervention)	Exploratory	The MLQ is a 10-item measure of meaning-in-life with 2 factors: Presence and Search. Cronbach’s α = 0.84-0.88 depending on subscale [53].*

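### The interpreting-error outcome is only a total count per Session 1, so it mixes accuracy with the amount of content interpreted; an error rate per content unit should stand beside it

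*Protocol article*

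**What the plan says.** The Key study objectives (second objective) state that the investigators "will compare the number of clinically significant interpreting errors in MCP-Ch Session 1 across RSMI and RCMI arms", and class this as a secondary outcome. Outcomes, Table 2 under Measures, and the Discussion also describe it as a number of errors. The Data analysis plan sets out two coding steps. A first blinded panel marks the clinically significant content in each transcript. A second blinded panel then looks for interpreting errors within that content, "yielding a total count of clinically significant interpreting errors". None of these places divides the total by content units, utterances, words or minutes.

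Three other statements bear on how much content a transcript can contain:

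- **Session length**, the same for all arms: "MCP-Ch consists of six 60-min individual sessions delivered over the span of 3–12 weeks" (Description of counseling sessions).
- **Timing of the two modes** (RSMI, RCMI, or bilingual provider): the RSMI interpreter "provides remote interpretation within milliseconds of the original speech, nearly simultaneously, almost like a voiceover", whereas the RCMI interpreter works "by listening as the primary speaker speaks and interpreting only once the primary speaker has finished".
- **The protocol's own expectation** (Background): "RSMI is likely superior to consecutive interpreting methods due to increased efficiency".

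**The concern.** A count per session is a fair measure of accuracy only if the sessions being compared offer similar numbers of opportunities for error. Here that number may depend on the interpreting mode itself. In RCMI each stretch of speech is followed by its rendering; in RSMI the two overlap. If both kinds of session last about an hour, an RSMI session can contain more source speech. Randomisation does not even this out, because the difference would be produced by the assigned mode.

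The error count is the trial's only direct measure of interpreting accuracy by mode. The Background expects fewer clinically significant errors with RSMI and reports that a systematic review found no quantitative studies of interpreter accuracy in mental health. The Data analysis plan intends the descriptive summaries to help design the definitive trial. A count without a denominator could hide an RSMI advantage per unit, or make it look like a disadvantage.

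**Working it through.** **The plan's own figures.** The protocol gives no sample size, expected count or error rate for this outcome, so there is nothing to reproduce for it. The only design calculation concerns feasibility: at least 11 of 15 completers, 40% against 90%, type I error 0.025, power 90%. It checks out (exact binomial type I error 0.0093, power 0.987) and does not involve interpreting errors.

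**Inputs from the protocol.** 15 participants in each interpreting arm, nominal 60-minute sessions, and the timing of the two modes.

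**Input that must be assumed.** E, the ratio of clinically significant content per session, RSMI to RCMI. Suppose session time is fixed, flagged content is proportional to source speech, and a consecutive rendering takes a fraction r of the time of the speech it renders. Then RCMI fits 1/(1 + r) of the content that RSMI fits, so E = 1 + r. A rendering as long as the source (r = 1) gives E = 2.0; r = 0.5 gives 1.5; r = 0.25 gives 1.25. If RCMI sessions simply run longer, or the flagged content is the same whatever the speaking time, E = 1.0.

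**Formula.** Raw count ratio = per-unit error-rate ratio × E. Counts tie when the per-unit rate ratio is 1/E.

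| E (assumed) | Count ratio at equal accuracy | Per-unit rate ratio at which counts tie | Count ratio if the true per-unit ratio is 0.70 |
|---|---|---|---|
| 1.0 | 1.00 | 1.00 | 0.70 |
| 1.25 | 1.25 | 0.80 | 0.88 |
| 1.5 | 1.50 | 0.67 | 1.05 |
| 2.0 | 2.00 | 0.50 | 1.40 |

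At E = 1.25, 1.5 and 2.0, RSMI would need a per-unit error rate 20%, 33% and 50% lower merely to tie. A true 30% advantage changes direction at E = 1.5 (0.70 × 1.5 = 1.05).

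**Would 15 sessions per arm show it?** A simulation took equal per-unit accuracy and an assumed mean of 10 errors per RCMI session. The table gives the share of simulated trials in which the RSMI mean count exceeds the RCMI mean.

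| E (assumed) | Poisson counts | Overdispersed counts (gamma-Poisson, dispersion 0.3) |
|---|---|---|
| 1.0 | 49% | 49% |
| 1.25 | 98% | 83% |
| 1.5 | about 100% | 96% |

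So if E differs from 1, even a descriptive comparison of arm means would usually point the wrong way on accuracy.

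**With a denominator.** Dividing errors by content units gives a ratio of 1.0 at equal accuracy for every E. Where E = 1.0, rate and count give the same ratio.

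**The case against.** The strongest reply is that unequal exposure is not documented. Sixty minutes is a nominal length; nothing says sessions are cut off there. Greater efficiency can equally mean the same content in less time. Errors are counted only in flagged content, and the examples given (such as cancer and psychiatric history, session exercises and later appointments) are largely agenda items of a manualised introductory session, which need not grow with words spoken. All of this stands, and it is why the assumed range must start at 1.0. It does not show that exposure is equal: history and exercises vary with the patient and the time available.

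Second, the arms are randomised, and the amount of content is a consequence of mode, not a confounder. The total number of errors a patient meets in a session is a legitimate quantity. This also stands, so the raw count should stay. Errors per unit answers a different question, how accurately each mode renders what is said, and it conditions on something that arises after randomisation.

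Third, the comparison is secondary and descriptive, the error tool is a cited one that cannot be checked here, and the plan lets coders refine the analytic approach during piloting. These points limit the consequences and leave room for the change. They do not supply a denominator.

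A reader might also infer that interpreter must be modelled because the same interpreters serve both arms. The documents do not support that: working in both modes limits any mixing of interpreter with mode, and an interpreter-adjusted count model suits neither a descriptive pilot nor about 30 sessions (2 × 15).

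**Conclusion.** The point holds in a limited form. The outcome is fixed as a total count, and the protocol's own account of the two modes makes unequal opportunity for error plausible, with any excess more likely in RSMI. As an accuracy comparison the raw count is therefore ambiguous: equal per-unit accuracy would show as a count ratio of 1.0 to 2.0 over the assumed content ratios of 1.0 to 2.0.

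A reader might go further and conclude that RSMI is penalised, or that a ratio of 1.5 or more is to be expected. The documents do not support either. They give no content or word counts per session, do not make 60 minutes a hard limit, and do not say that flagged content scales with speech. No distortion at all remains possible. The primary feasibility outcome and the traffic-light progression rule rest on session completion and are unaffected.

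**What to change.** In objective 2 of the Data analysis plan:

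- Keep the raw count, described as errors met per session.
- Add errors per 100 clinically significant content units, with the content identified by the first panel as the denominator. State what counts as one unit, defined on the source speech so that it means the same in both modes.
- Summarise both descriptively by arm, with the number of content units and session minutes alongside.
- Base statements about relative interpreting accuracy on the rate.

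An RSMI/RCMI rate ratio with a 95% confidence interval is optional; no interpreter fixed-effect model is needed. The cost is a few lines of wording and slight extra tabulation, because the coding that yields the denominator is already planned.

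### Inter-rater reliability is to be calculated as percent agreement, but the threshold for starting the main coding is k = 0.80, a chance-corrected statistic the plan never says it will calculate

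*Protocol article*

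**What the plan says.** The relevant text is in the protocol article, Data analysis plan (by objective), objective 2. Interpreting errors in MCP-Ch Session 1 are coded in two steps.

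- **Content panel.** For this step, "a panel of 2–4 psycho-oncology clinicians blinded to the interpreting method (i.e., RSMI or RCMI) will review and code transcripts". The clinicians mark clinically significant content and then meet to reconcile their selections.
- **Error panel.** Next, "a second blinded panel of 2–4 bilingual coders will independently code clinically significant content to identify interpreting errors". The article describes the product of this second step as "yielding a total count of clinically significant interpreting errors".

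Before the main coding, "coders on both panels will first separately conduct preliminary analyses on a subset of transcripts using the described protocol". On reliability the article then says two things in succession:

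- "Interrater reliability will be assessed by calculating percent agreement".
- Consensus meetings settle disagreements and refine the categories "until strong interrater reliability is reached (i.e., *k* = 0.80"). Reaching that value is what releases the coders: "at which point coders will commence coding of the remaining transcripts".

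The symbol k is not defined there or in the abbreviations list. No calculation of kappa or any other chance-corrected measure is described anywhere in the article.

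**The concern.** Percent agreement and kappa are different statistics. Percent agreement counts agreement that would arise by chance; kappa removes it. The article says one will be calculated and sets its decision threshold on the scale of the other. A coding team following the text has only percent agreement in hand when it asks whether 0.80 has been reached, so the easy slip is to accept 80% agreement.

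The number of clinically significant errors is a secondary outcome, and it is the trial's only direct measure of interpreting accuracy. Accuracy is part of the rationale for RSMI given in the Background, and the summaries by arm are meant to inform the definitive trial. The threshold is the only quantified reliability safeguard on this outcome, and passing it releases the coders to all remaining transcripts.

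**Working it through.** **Inputs from the article.** Statistic to be calculated: percent agreement. Threshold: k = 0.80. Panels: 2–4 coders each, coding independently. The 0.80 is a chosen threshold, so there is no derived figure to reproduce.

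**Assumptions.** Two coders, a yes/no code per unit, and the same flagging rate p for both. The article gives neither a flagging rate nor a coding unit, so p is varied from 2% to 50%. Results for rates above 50% mirror those below.

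**Formulas.**

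- Chance agreement: Pe = p² + (1 − p)²
- Kappa at observed agreement Po: κ = (Po − Pe)/(1 − Pe)
- Agreement needed for κ = 0.80: Po = Pe + 0.80(1 − Pe) = 0.80 + 0.20 Pe
- Lowest possible agreement: 1 − 2p for p up to 50%

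The third formula shows that 80% agreement equals kappa 0.80 only if chance agreement is zero. With equal flagging rates Pe is never below 0.50, so kappa 0.80 always needs at least 0.80 + 0.20 × 0.50 = 90% agreement.

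**Worked example, p = 10%.** Pe = 0.01 + 0.81 = 0.82. At 80% agreement, κ = (0.80 − 0.82)/0.18 = −0.11. At 90% agreement, κ = 0.08/0.18 = 0.44. For κ = 0.80, Po = 0.80 + 0.20 × 0.82 = 96.4%.

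| Flagging rate p (assumed) | Chance agreement | Lowest possible agreement | Kappa at 80% agreement | Agreement needed for kappa 0.80 |
|---|---|---|---|---|
| 2% | 96.1% | 96% | not attainable | 99.2% |
| 5% | 90.5% | 90% | not attainable | 98.1% |
| 10% | 82.0% | 80% | −0.11 | 96.4% |
| 15% | 74.5% | 70% | 0.22 | 94.9% |
| 20% | 68.0% | 60% | 0.38 | 93.6% |
| 30% | 58.0% | 40% | 0.52 | 91.6% |
| 50% | 50.0% | 0% | 0.60 | 90.0% |

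**Where 80% agreement is no better than chance.** Setting Pe = 0.80 gives 2p² − 2p + 0.20 = 0, so p = (1 − √0.6)/2 = 11.3%. At or below that rate, coders flagging at random are expected to reach 80% or more. At 10% or below, agreement cannot fall under 80%, so an 80% threshold could not be failed.

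**Exposure.** With 15 participants in each of the two interpreting arms there are about 30 Session 1 transcripts, less the calibration subset, whose size is not given. The content panel reconciles its differences in any case. For the error panel, consensus meetings are described only up to the threshold, and no reliability check is described after it.

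**The case against.** The strongest reply is that the threshold as written is k = 0.80, and a kappa of 0.80 cannot be met by near-chance coders. An 80% agreement threshold appears nowhere in the article. On the kindest reading, percent agreement is reported, kappa decides release, and one sentence is missing. This stands as a possible reading, but the article does not state it: the only statistic it says will be calculated is percent agreement.

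Three stronger readings are tempting, and the article does not support them.

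- **Coders will be released at near-chance agreement.** This needs 0.80 to be applied to percent agreement and also a flagging rate of about 11% or less. The error panel codes only content already selected as clinically significant, so its rate may be higher. The content panel selects content, not errors, so rarity of errors does not describe its task. The −0.11 at 10% is also the extreme case, in which the two coders never flag the same unit; consensus meetings would expose that before release.
- **The threshold cannot be evaluated.** Both panels code independently, so kappa can be computed from the codes already planned.
- **The comparison of RSMI with RCMI is pulled towards no difference.** The outcome is a count. If the modes yield different amounts of coded content, false positives would scale with that content, and the bias could go either way.

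It is also fair that a condensed article may leave the choice of coefficient to a coding manual. That does not cover naming one statistic and setting the threshold on another.

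**Conclusion.** The mismatch is real, and nothing elsewhere in the article resolves it. Its practical effect depends on how the team applies the threshold. If kappa is computed and held to 0.80, the defect is one of wording only. If 0.80 is read on percent agreement, the standard is laxer at every flagging rate: coders would be released at 80% agreement where kappa 0.80 needs between 90.0% (half of units flagged) and 99.2% (2% flagged). At flagging rates of 20% to 50% that is a lax standard, not a near-chance one. These figures rest on two coders, a binary code and equal flagging rates, and the rates themselves are assumed.

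The likely harm is added measurement error, of uncertain direction, in the error panel's counts for the remaining Session 1 transcripts. The outcome is secondary and summarised descriptively. The feasibility rule and the progression criteria depend on session completion and are unaffected. The point deserves correction because the remedy is nearly free.

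**What to change.** Replace percent agreement as the deciding statistic with a chance-corrected one, and define k. Compute it on the independent codes before any consensus discussion, separately for each panel: Cohen's kappa if there are two coders, Fleiss' kappa or Krippendorff's alpha if there are three or four. Apply the 0.80 threshold to that statistic, worded as at least 0.80, and report percent agreement as a supplement.

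This is about one sentence of text and uses codes that will be collected anyway. The one real cost is that a stricter standard may require an extra calibration round before the main coding begins.
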